### Participant timeline {13}

A schematic diagram of the time schedule for the participants is shown in Fig. 2.

**Fig. 2 Fig2:**
[figure not shown]
Schedule of enrollment, intervention, and assessments for participants

### Sample size {14}

This is the first study to simultaneously examine the effects of a brown rice-derived supplement on physical, cognitive and mental health; therefore, determining a uniquely valid sample size is not possible. Instead, we determined the sample size for this study (i.e., 40 participants in each group) by referencing an RCT that examined the effect of processed brown rice products on health, including the gut microbiota [13]. We will recruit 96 participants to allow for a potential 20% dropout rate.

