**Methods:**

This study will be a prospective, longitudinal, double-blind, randomized, placebo-controlled trial. Eighty healthy adults aged 20 to 64 years will receive 3.5 g/day of a brown rice-derived supplement or placebo for 12 weeks. We will assess immune-related and metabolic markers using transcriptome and metabolome analyses of blood samples, respectively, and evaluate the gut microbiota composition using stool samples, including 16S rRNA-based analysis, with short-chain fatty acids also measured. Cognitive function, constipation, sleep, mood state, and health-related quality of life will also be assessed using validated assessments at baseline and at the endpoint. Between-group comparisons will be conducted using appropriate statistical methods according to the distribution and characteristics of the data.

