### Trial design {8}

This study will be a longitudinal, double-blind, randomized, placebo-controlled prospective intervention trial with a parallel group of healthy adults (see Fig. 1 for an overview of the planned trial design). We designed this study to explore the effects of brown rice-derived supplementation on various health outcomes, including the immune system, cognitive function, gut microbiota, constipation, sleep, and HRQOL. Participants will be randomly assigned to the brown rice-derived supplement group or the placebo group at a ratio of 1:1. This protocol is in accordance with the Standard Protocol Items: Recommendations for Interventional Trials checklist [30]. This study protocol was approved by the Ethics Committee of Tohoku University Graduate School of Medicine (IRB# 2022–1–845) and preregistered in a clinical trial registry (UMIN-CTR ID: UMIN000049330). The committee has peer-reviewed the progress of the study, independent of our research team.

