### Recruitment {15}

We will recruit all participants by posting an advertisement in a community information magazine that is freely distributed in Sendai City and surrounding cities in Miyagi Prefecture, Japan. Individuals who are willing to participate in the trial will be asked to access the website with detailed information via a QR code. Cash (7000 yen, if all protocols are completed) will be offered as remuneration for all participants. Recruitment will be conducted in three phases, with approximately 32 participants recruited per phase.

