### Methods in analysis to handle protocol non-adherence and any statistical methods to handle missing data {20c}

The primary analysis will be based on the intention-to-treat (ITT) principle, but we will include only the randomized participants who participate in data collection at both the baseline and the study endpoint, irrespective of their degree of adherence to experimental food consumption. In this study, we will exclude randomized participants who drop out of the study and do not provide endpoint data, as this study aims to examine the effect of the nutritional supplement on healthy adults, and we do not expect as great an effect as when medication is administered to a patient group. To follow the ITT principle as closely as possible, all the participants will be asked to participate at the endpoint as much as possible. A per-protocol analysis limited to participants with adherence ratios greater than 80% will be performed as a sensitivity analysis. Every effort will be made to prevent missing values during the data collection process, and we will address any missing data using multiple imputation or regression imputation.

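### Recruiting 96 does not cover 20% dropout from a target of 80: about 77 would remain, and a 20% allowance needs 100

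*Protocol article*

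**What the plan says.** In the protocol article, Sample size {14} fixes the target by reference to an earlier trial of processed brown rice products: "we determined the sample size for this study (i.e., 40 participants in each group". The same section then gives the allowance for loss: "We will recruit 96 participants to allow for a potential 20% dropout rate". Recruitment {15} is consistent with that total: "Recruitment will be conducted in three phases, with approximately 32 participants recruited per phase".

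The Methods paragraph of the abstract uses only the lower figure: "Eighty healthy adults aged 20 to 64 years will receive 3.5 g/day of a brown rice-derived supplement or placebo for 12 weeks". Allocation is equal (Trial design {8}): "Participants will be randomly assigned to the brown rice-derived supplement group or the placebo group at a ratio of 1:1".

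The section on non-adherence and missing data {20c} decides who counts in the primary analysis: "we will exclude randomized participants who drop out of the study and do not provide endpoint data".

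**The concern.** The sentence on dropout is there to protect the target of 40 per group. It looks like the common slip of inflating by multiplying by (1 + rate) when the target should be divided by (1 − rate). If so, the trial misses its own target at its own assumed dropout rate.

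The analysis rule makes this more than a matter of presentation. Under section {20c} a participant who drops out and gives no endpoint data is removed from the primary analysis. The imputation mentioned in the same section does not bring that person back. Each such loss therefore comes straight off the analysed number.

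The abstract adds a smaller difficulty. It gives eighty as the number who will receive product, with no mention of the 96 to be recruited. A reader of the abstract alone cannot tell that eighty is the number the trial hopes to have left after dropout.

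**Working it through.** **Inputs**

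- Target: 40 per group, so 2 × 40 = 80 (Sample size {14}).
- Number to be recruited: 96 (Sample size {14}), which agrees with 3 × 32 = 96 (Recruitment {15}).
- Assumed dropout: 20% (Sample size {14}).
- Allocation: 1:1 (Trial design {8}).
- Participants without endpoint data: excluded from the primary analysis (section {20c}).

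**1. Reproduce the stated figure.** Target × (1 + rate) = 80 × 1.20 = 96. This matches exactly.

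**2. Inflate for dropout among those who enter.** Target / (1 − rate) = 80 / 0.80 = 100. This does not match; the stated figure is 4 short.

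**3. Check in reverse.** 96 × (1 − 0.20) = 76.8, about 77. With equal allocation and equal dropout, 76.8 / 2 = 38.4, about 38 per group. The shortfall is 80 − 76.8 = 3.2 participants, and 3.2 / 80 = 4%.

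**4. Dropout that 96 can absorb.** 1 − 80/96 = 16.7%.

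**5. Chance of reaching the target.** As an illustration, assume that each participant drops out independently with probability 20%. The binomial probability of at least 80 completers is then about 0.25 with 96 recruits and about 0.56 with 100.

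**The case against.** The best defence of 96 reads the 20% as a share of the target: 20% of 80 is 16, and 80 + 16 = 96. That explains how the number arose, but it does not make the statement right. A dropout rate describes what fraction of entrants is lost, and on that meaning 96 covers 16.7%.

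A second defence is that the recruitment plan is only approximate. One hundred participants would mean about 33.3 per phase (100 / 3) where about 32 is planned, a difference within the looseness of the wording. That shows how little separates the two numbers in practice. But three phases of about 32 still total about 96, and the Sample size section states 96 without qualification.

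A third objection concerns weight, and it stands. The article says that "determining a uniquely valid sample size is not possible" and gives no significance level, power, effect size or standard deviation. A reader might infer that the trial falls below its planned power. The document does not support that, because there is no planned power to fall below. Purely for scale, assume a single unadjusted comparison of means at two-sided 5% with 80% power at 40 per group: power at 38 per group would be about 78%. These assumptions are not the protocol's, which has several co-primary outcomes and covariate-adjusted analyses.

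Two further inferences also go too far. A reader might take it as fixed that 96 will be randomised, split exactly in half. The article speaks only of recruiting 96 and of a 1:1 ratio; it gives no randomised total and no number allocated per group. A reader might also call the abstract a contradiction of the body. It is better described as a loose condensation: eighty agrees with the target of 40 per group, and the Sample size section shows how 80 and 96 are related.

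**Conclusion.** The point holds. As written, the Sample size section claims an allowance that its own numbers do not provide: 96 recruits cover 16.7% dropout, and at 20% about 77 participants (about 38 per group) would remain where 80 (40 per group) are intended. The exclusion rule in section {20c} places that loss in the primary analysis set.

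The effect is small, about 3 analysed participants or 4%. It changes no feature of the design or analysis and supports no claim that the trial is underpowered. It is still worth correcting, because 40 per group is the only numerical basis the article gives for the size of the trial.

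The conclusion rests on the usual meaning of a dropout rate, as a fraction of those who enter. It also takes dropouts to be people without endpoint data, who are the ones section {20c} excludes. The figure per group further assumes equal allocation and equal loss in both groups. Nothing outside the document is needed.

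**What to change.** Restate the allowance in Sample size {14}, for example:

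> 96 participants will be recruited; this keeps the target of 80 completers (40 per group) if dropout is at most 16.7%; at 20% dropout about 77 (about 38 per group) would remain.

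In the abstract, describe 80 as the target number of completers and 96 as the number to be recruited. Eighty should not be called the number expected to complete, since about 77 are expected at the stated 20%.

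Add no power statement, because the plan gives no basis for one, and no fixed number randomised per group, because none is given.

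The cost is a few words in two places, plus a stated allowance that looks slightly less generous. If the investigators want to cover 20% in full, the alternative is to recruit 100, four more than planned. Trial status reports recruitment under way since February 2023, so restating the allowance is the proportionate course.

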### Recruitment {15}

We will recruit all participants by posting an advertisement in a community information magazine that is freely distributed in Sendai City and surrounding cities in Miyagi Prefecture, Japan. Individuals who are willing to participate in the trial will be asked to access the website with detailed information via a QR code. Cash (7000 yen, if all protocols are completed) will be offered as remuneration for all participants. Recruitment will be conducted in three phases, with approximately 32 participants recruited per phase.

### Sequence generation {16a}

Participants will be randomly divided into a brown rice-derived supplement group and a placebo group at a 1:1 ratio by computer-assisted random number generation. To maintain double-blind conditions, neither the examiner nor the participants will have any information regarding which group they are allocated to during the study.

### Concealment mechanism {16b}

The information on the allocation of participants will be kept in a tightly sealed envelope and locked in a locked cabinet that is inaccessible to the examiner. The envelopes will be checked weekly by a laboratory staff member who will not participate in the trial and who has a desk in a separate room from the examiner. Allocation concealment will be guaranteed by the above procedures.

### Implementation {16c}

The participants will be allocated to groups by staff members who will not otherwise participate in the examination. Other technical staff in the laboratory will prepare the respective interventions and put them in the bags that will be given to participants on the basis of allocation numbers, but the numbers will not include information about the supplement or placebo.

## Assignment of interventions: blinding

### Who will be blinded {17a}

All involved parties, including participants and research staff members responsible for the allocation and assessment of outcomes, will be blinded, as the supplement and placebo will arrive having already been packaged, with only the identifying numbers printed on the products.

### Procedure for unblinding if needed {17b}

If severe adverse effects or allergic reactions occur, the consumption of the brown rice-derived supplement or placebo will immediately be stopped. If the principal investigator judges that knowledge of allocation might be beneficial for the participant’s safety, the sealed envelopes containing the table regarding assignment will be opened, and the individual assignment of the participant will be revealed to report severe adverse effects and allergic reactions by the research staff managing the table. After such reports are provided, the table will be strictly resealed and maintained.

## Data collection and management

### Plans for assessment and collection of outcomes {18a}

#### Immune function

PBMCs will be collected using BD Vacutainer® CPT™ Mononuclear Cell Preparation Tubes with sodium citrate (BD Bioscience, USA) according to the manufacturer’s instructions. Then, total RNA will be extracted from PBMCs using an RNeasy Mini Kit with an RNase-Free DNase Set (Qiagen, Venlo, Nederland). RNA-seq libraries will be generated using the NEBNext Globin & rRNA Depletion Kit and the NEBNext UltraII Directional RNA Library Prep Kit (New England Biolabs, MA, USA) according to the manufacturer’s instructions. Sequencing experiments will be performed with a NextSeq 500 (Illumina; High Output Kit v2.5, 75 cycles). The obtained reads will be mapped to the human genome grch38 and processed using fastp (removing reads with < Q30), HISAT2, SAMtools, and featureCounts [34–37]. The obtained TPM scores will be subjected to identification of differentially expressed genes (DEGs) [38], gene ontology analysis [39], estimation of immune cell contents [40], and weighted gene coexpression network analysis [41]. The data will be represented according to the examples described in our previous publications [42–46].

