### Outcomes {12}

Previous studies have suggested that brown rice has various effects on human health, and we will present evidence concerning these effects and the underlying mechanisms by using a brown rice-derived supplement in this study. Therefore, the overall condition of the immune system, metabolism, constipation, sleep, cognitive function, mental health, and gut microbiota community composition will be co-primary outcomes for comprehensively examining various health aspects. Blood samples will be collected to analyze immune function and metabolism via transcriptome and metabolome analysis, respectively, and stool samples will be collected to evaluate diversity in the gut microbiota.

In addition, we will collect information on the factors that may influence the relationships between consumption of the brown rice-derived supplement and primary outcomes. Various lifestyles could influence the relationships between the consumption of the brown rice-derived supplement and broad health conditions. In particular, daily eating habits and physical activity may strongly impact these relationships. Therefore, we use the brief-type self-administered diet history questionnaire (BDHQ) and a simple questionnaire to evaluate total and domain-specific physical activity [31, 32]. In addition, we will collect data on the overall intelligence quotient (IQ) to control for the influence of IQ on the performance of cognitive tests [33].

Since this study aims to determine the effects of brown rice-derived supplement consumption on various health aspects, all sample collection and measurements, except for daily health, will be performed at two time points (baseline and endpoint), and we will compare the changes in these variables between and within groups. Daily health during the intervention period will be compared between groups. We assume that these variables will change in a positive direction if the brown rice-derived supplement is effective at improving human health.

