## Statistical methods

### Statistical methods for primary and secondary outcomes {20a}

The co-primary outcomes will be analyzed to determine whether the consumption of the brown rice-derived supplement is superior to the use of a placebo in terms of positive health effects. The data derived from transcriptome and metabolome analysis will be compared between intervention groups after relevant covariates are controlled for. Microbiome and overall community composition will be compared between intervention groups on the basis of alpha and beta diversity with relevant covariates controlled for. For cognitive function, all outcomes will be compared through an analysis of covariance, with the intervention group set as a between-group factor, the data collection time points as a within-group factor, and the covariates as relevant covariates. The BMI and questionnaire data will be compared through an analysis of covariance controlling for relevant covariates. For continuous variables, the distribution of the data and the fulfillment of the model assumptions will first be assessed. Parametric methods will be used when the relevant assumptions are met; otherwise, appropriate nonparametric methods will be applied.

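### Differential expression is specified on TPM although raw read counts are available; unchanged genes can be miscalled if transcript composition differs between arms

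*Protocol article*

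**What the plan says.** In the protocol article, Immune function (under Plans for assessment and collection of outcomes {18a}), the material is bulk PBMC RNA: "total RNA will be extracted from PBMCs using an RNeasy Mini Kit". The reads are "processed using fastp (removing reads with < Q30), HISAT2, SAMtools, and featureCounts". The next sentence fixes the input to the downstream work: "The obtained TPM scores will be subjected to identification of differentially expressed genes (DEGs"). The same sentence puts gene ontology analysis, "estimation of immune cell contents" and co-expression network analysis on that input.

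Statistical methods for primary and secondary outcomes {20a} adds only this: "The data derived from transcriptome and metabolome analysis will be compared between intervention groups after relevant covariates are controlled for". The section on biological specimens {33} refers back to Immune function for the data analysis.

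Outcomes {12} lists the immune system among the co-primary outcomes and ties it to this assay: "Blood samples will be collected to analyze immune function and metabolism via transcriptome and metabolome analysis, respectively".

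**The concern.** TPM values in a sample always add to one million. A gene's TPM therefore depends on every other gene in that sample. If one arm has more of some abundant transcripts, the TPM of all other genes must fall in that arm, and a between-arm test can read the fall as regulation. PBMCs are a mixture of cell types, and the protocol plans to estimate that mixture, so it treats composition as something that may vary.

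TPM also divides out sequencing depth and gene length. A value based on 5 reads and one based on 1,000 reads can look the same, so a model can no longer give each its proper weight. featureCounts produces gene-level counts one step earlier, so the better input already exists.

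At stake is how far the gene list, and the ontology results built on it, can be trusted as evidence on a co-primary domain.

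**Working it through.** The protocol gives no SD, effect size or error rate for the transcriptome, so there is no stated figure to reproduce. The check is of the mechanism and its possible size.

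**Inputs from the document.** Sample size {14} plans "40 participants in each group", with 96 recruited and 20% dropout allowed for. That leaves 96 × 0.8 / 2 = 38.4, or about 38 per arm.

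**Assumed inputs.** These are the share *s* of the TPM total held by the genes that rise (close to, but not identical with, their share of reads), the fold change *f*, and the per-gene SD in log2 units. None of them is in the document.

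**Step 1: shift of an unchanged gene.** The total before rescaling grows by the factor 1 + s(f − 1), so an unchanged gene moves by −log2(1 + s(f − 1)). For f = 1.5:

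- s = 5%: −log2(1.025) = −0.036
- s = 10%: −log2(1.05) = −0.070, a fall of about 5%
- s = 20%: −log2(1.10) = −0.138

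**Step 2: chance of nominal p < 0.05 for that gene.** SE = SD × √(2/38), which is 0.069 for SD 0.30 and 0.103 for SD 0.45. For s = 10%, the shift is 0.0704/0.0688 = 1.02 SE and 0.0704/0.1032 = 0.68 SE. Adding both tails gives about 17.5% and 10.5%. Simulated t-tests on null genes gave:

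| Share s (f = 1.5) | SD 0.30 | SD 0.45 |
|---|---|---|
| 5% | 8.2% | 6.5% |
| 10% | 17.5% | 10.5% |
| 20% | 50.8% | 25.8% |

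With 40 per arm, s = 10% and SD 0.30, the normal formula gives 18.3%. At SD 0.50 it gives 9.7%.

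**Step 3: does using counts help?** Negative-binomial data were simulated for 4,000 genes and 40 per arm, with dispersion 0.08 (roughly √0.08/ln 2 = 0.41 log2) and a median library of 5 million reads. A t-test on log2(TPM + 1) was compared with a t-test on log2 counts scaled by median-of-ratios. The rates are for unchanged genes with above-median expression. The full count model recommended below was not itself simulated.

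| Scenario | TPM, p < 0.05 | Scaled counts, p < 0.05 |
|---|---|---|
| No composition difference | 4.9% | 4.8% |
| Few abundant genes (0.9% of genes, 9% of reads) up 1.5-fold | 9.8% | 4.8% |
| Few abundant genes (1.7% of genes, 19% of reads) up 1.5-fold | 21.0% | 5.1% |
| Few abundant genes (1.5% of genes, 19% of reads) up 2-fold | 57.1% | 5.4% |
| About 20% of genes up 1.5-fold together | 28.9% | 22.1% |
| About 22% of genes up 2-fold together | 80.7% | 56.2% |

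Scaling removes the artefact when a small set of abundant genes moves. It removes only part of it when many genes move together.

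**Step 4: precision.** The sampling CV of a count with mean μ is 1/√μ: 45% at 5 reads, 22% at 20, 10% at 100 and 3% at 1,000. TPM alone does not show which applies. The resulting loss of power was not calculated.

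**The case against.** The strongest defence is that the sentence is shorthand. It puts four analyses under one subject and leaves the differential-expression method to a cited source that is not shown. If that method takes counts, the text is loosely worded and the analysis may be sound. An article may also leave the model and normalisation to an analysis plan. This stands as far as it goes: a missing model name is no finding. But the input is stated, it is TPM, and nothing in {20a} or {33} alters it. The sentence needs correcting in either case.

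Second, the error rates rest on assumed shifts. The section on non-adherence and missing data {20c} itself expects a smaller effect than from medication in patients. A reader might infer that 11 to 18% is the error rate to expect. The document does not support that: it gives no share, fold change or SD, and without a composition difference TPM holds its level. The rates are also nominal and per gene, and nothing here shows the effect after false-discovery control.

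Third, a reader might infer that moving to counts cures the cell-mix problem. It does not. A changed mix alters bulk expression for real, in counts as in TPM, and Step 3 shows only partial correction when many genes move. This objection stands in full and shapes the fix.

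Fourth, differential expression is one of several transcriptome analyses, and the planned cell estimation would itself help to reveal a composition shift. So the point does not undermine the whole immune outcome, nor does it apply to TPM as input for cell estimation.

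**Conclusion.** The point holds in a limited form. As written, the protocol tests differential expression on a closed proportion although the counts are available. This can move unchanged genes if transcript composition differs between arms, and it discards information on precision. Under assumed values (10% share, 1.5-fold rise, SD 0.30 to 0.45 log2, about 38 per arm) the shift is −0.07 log2 and the nominal per-gene false-positive rate is about 11 to 18%. At a 5% share it is about 6 to 8%, and with no composition difference about 5%. These figures show what could happen and are not a forecast for this supplement. The loss from discarded precision is real in principle but not quantified. The correction is worth making because the gene list informs a co-primary domain and the change costs almost nothing.

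**What to change.** Amend the sentence in Immune function so that differentially expressed genes are called on the featureCounts gene-level counts, with between-sample normalisation (TMM or median-of-ratios), in a negative-binomial model or a precision-weighted log-count model. State that TPM is kept for immune-cell estimation and display. If the cited method already takes counts, the amendment simply says so.

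Add a sensitivity analysis of differential expression that adjusts for the immune-cell proportions already being estimated. Genes that lose their signal after adjustment should be reported as possibly reflecting cell mix.

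The cost is one or two sentences and some extra analysis code, with no new samples or assays. The change should be fixed before any unblinded analysis.
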